### Safety

For the clinical laboratory test data, depending on the nature of the variables, ANOVA, *t* test, chi-squared, or Fisher’s exact test will be conducted. The 95% confidence interval for the number of AEs and the percentage of patients who may experience one or more AEs will be calculated within groups and compared between groups. In the case of safety assessment variables, the missing values will be analyzed as missing.

### Data management and monitoring

Paper CRF files will contain all records. The CRF files will be stored in a securely locked location. Participant identification and privacy information will be deleted from all study documents to protect confidentiality. Once the trial is completed, a double independent data entry will be conducted to promote data quality. After the data entry is finished, the database will be locked and analyzed by an independent statistician under the supervision of the PI. Site investigators will have the right to directly access the final datasets from their own sites.

According to the guidelines for establishing and operating an Independent Data Monitoring Committee (IDMC), written by the Korean Ministry of Food and Drug Safety (MFDS) [12], based on guidelines by the US Food and Drug Administration (FDA), World Health Organization (WHO), and Europe, the Middle East, and Africa (EMEA) in Europe, not all clinical trials require an IDMC. The effectiveness of an IDMC is very low in clinical trials in non-fatal indications, where patients are treated for relatively short periods of time and the characteristics of the drug being tested are well defined and known not to cause harm to the patient. In this clinical trial, OKT will be administered orally for a short period of 8 weeks, and the OKT product was already approved for use for coldness of the lower limbs. Thus, it was determined that an IDMC is not needed. Nevertheless, instead of an IDMC, the K-CTC will monitor the institutions conducting the clinical trial based on the SOPs while the trial is in progress to control data quality. When the first patient finishes the necessary visits, the monitoring will begin. Double data entry and range checks for data values will be conducted to improve the quality of data. No auditing is scheduled for this study.

## Discussion

From the perspective of conventional medicine, CHHF presents clinical symptoms of Raynaud’s phenomenon (RP), which is categorized as a peripheral vascular disease. Therefore, patients with CHHF are mostly prescribed vasodilators or antihypertensive drugs. In contrast, in Eastern medicine, coldness is considered as one of the major pathogenic factors. Therefore, the primary treatment principle of CHHF in Eastern medicine is to balance the Yin and Yang energy of the body with personalized and holistic approaches [13].

OKT was named for its warming, tonifying, enriching, and nourishing effects [9]. It consists of 11 components, including *Evodiae Fructus*, *Ginseng Radix Alba*, *Paeoniae Radix*, *Asini Corii Colla*, *Cnidii Rhizoma*, *Pinelliae Tuber*, *Moutan Cortex Radicis*, *Liriopis Tuber*, *Angellicae Gigantis Radix*, *Zingiberis Rhizoma*, and *Glyzzirizae Radix*. Among these, *Ginseng Radix Alba*, *Asini Corii Colla*, and *Liriopis Tuber* are used to tonify Qi, engender fluids, and tonify Yin. *Angellicae Gigantis Radix* and *Cnidii Rhizoma* play a role in harmonizing the blood. *Paeoniae Radix* and *Glyzzirizae Radix* harmonize nutrients, and *Pinelliae Tuber* warms the middle part of the body to harmonize the stomach. *Moutan Cortex Radicis* cools the blood, dissipates stasis, and unblocks the meridian. *Zingiberis Rhizoma* and *Evodiae Fructus* warm and tonify the life gate [14]. In particular, *Ginseng Radix Alba* is known for its remarkable adaptogenic quality of helping the body to adapt to cold, fatigue, and stress. Previous trials demonstrated that *Ginseng Radix Alba* considerably enhances the body’s capacity to cope with extreme temperatures, emotional and mental stress, and hunger. *Angellicae Gigantis Radix* is a warming herb that improves blood circulation to the hands, feet, and abdomen [15]. Through the combined effects of these herbs, OKT warms and nourishes the meridian to dissipate cold and is widely used clinically in the treatment of gynecological diseases and coldness in the body. OKT has been reported to have clinical efficacy in the treatment of ovulation disorders, vaginal bleeding, and infertility [16–18]. *Jin kui yao lue*, a textbook of Chinese herbal medicine, states that OKT improves coldness in the lower body of women as well as infertility and ovulation disorders, as mentioned above. One study using a laser Doppler fluxmeter demonstrated that OKT treatment significantly increased peripheral blood flow in the lower extremities of patients with coldness [19]. The OKT granules used in this clinical trial are also recommended for relieving coldness of the lower extremities. According to a Delphi study for the treatment standardization of coldness in the hands and feet, OKT is a commonly used medicine for CHHF in practice in both decoctions and extracts (granules) [6]. Thus, we decided to prescribe OKT to study CHF.

This study has some strengths and limitations. This will be the first RCT to evaluate the efficacy and safety of OKT in treating CHF symptoms. The PubMed database revealed four studies when searched with “*wen jing tang*”. A total of 688 papers were searched on the Chinese database China National Knowledge Infrastructure CNKI using the search word “*温经汤* (*wen jing tang*)” and 127 papers were searched using the search word “*温经汤* (*wen jing tang*) *and 寒* (*coldness*)”. Searching the Korean database OASIS revealed 10 articles which showed the results of domestic research on OKT. There were many studies on the effects of OKT on gynecological diseases and coldness, but there were no RCTs to examine the safety and efficacy of OKT for CHF. This study has another strength: specifically, the team members engaged in this clinical trial are familiar with the SOPs of this study, as they were part of a previous pilot study that investigated the effects of *Danggui-SayukGa-Osuyu-Saenggang-tang* [20], *Ojeok-san* [21], or *Sipjeondaebo-tang* [22] on CHHF.

However, this study has a few limitations. First, a few participants in this trial are likely to be able to distinguish subtle differences between the placebo and test drugs, because they may have been a participant in similar clinical trials at the recruiting hospital. Second, because CHHF is a disease that is easily affected by cold weather, it is possible that changes in weather may have an influence on the outcomes. Therefore, although the BT measurement and the CST are performed after a relaxation period of 20 min at 24 ± 1 °C in the examination room, warmer weather is likely to produce better results, and colder weather may negatively affect the results. Furthermore, we could not fully exclude other underlying diseases that cause CHHF, because laboratory tests such as the antinuclear antibody (ANA) test could not be performed due to the small size of our research grant. Additionally, because the pathogenesis of CHHF is not clear, all of the CHHF-related diseases are not fully known. Finally, this study sets the criteria for dropout, which may affect the results of this study. For example, those who have used medications or treatments that may have effects on the symptoms of CHF, such as anticoagulants and psychotropic drugs, will be withdrawn. Nevertheless, those who take other medications may have taken them because OKT had not improved their symptoms. As such, when we drop out the subjects with low therapeutic effect, it may influence the results of the study. Nevertheless, efficacy data will be analyzed based on the ITT analysis; therefore, dropout is very unlikely to translate into better results, and in general, the more dropouts, the lower the cure rate. Among the forbidden drugs, anticoagulants were contraindicated, because the body temperature can be increased due to the blood flow-improving effects of anticoagulants. Drugs for hyperthyroidism and antipyretic analgesics were prohibited because they can affect the body’s heat metabolism. Psychotropic drugs were prohibited because they may cause problems related to research ethics. In addition, those whose compliance is less than 70% will be withdrawn. During the clinical trial period, compliance should be monitored to guarantee the power of the study. Compliance data are helpful for the interpretation of trial results to avoid erroneous conclusions and to enrich the value of the results [23]. High levels of non-compliance in a clinical trial may provoke the risk of a type II error (also called beta error or manufacturer’s risk). This is the risk of finding no meaningful difference in drug action between the test drug and control when there is a real difference. Increasing the sample size can reduce this risk; however, it will induce an increase of the expense in trial cost [24]. If the compliance is less than 70%, the effect of the OKT formulation can be lowered, and the result of the study may not be accurate; therefore, those with low compliance will be withdrawn. Poor compliance was also suggested as a dropout criterion in other clinical trials studying PURIAM110 (a dietary supplement) [25], Korean red ginseng [26], and Taeumjowi-tang (a traditional Korean medicinal extract) [27], among others. Other requirements are also proposed as dropout criteria because they may affect ethical issues or research accuracy. Although these criteria may have some impact on the outcome of the study, they were presented to comply with research ethics and to verify the effect of the research medication itself.

In spite of these limitations, the current study should add valuable information to the medical literature, as it is the first clinical trial to assess the efficacy and safety of OKT for the treatment of CHF. We anticipate that this study will provide evidence for treating CHF symptoms with the herbal medicine OKT, and that this clinical trial protocol will offer basic data for designing a further large-scale RCT.

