### Statistical analysis

The basic statistical analysis method will be the degree of change in the efficacy assessment index between the results of the baseline tests performed before the administration of the test drug and the results of the tests at the end of treatment. The statistical significance level will be set at *P* < 0.05. SPSS for windows version 25.0 (IBM Inc., Chicago, IL, USA) will be used for performing the statistical analysis.

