#### Efficacy

For the efficacy assessment, ITT analysis, a method for including all randomly assigned patients in the analysis regardless of violation or dropout, will mainly be used. Per-protocol (PP) analysis, a method which excludes subjects who do not comply with the study protocol or who have missing data, will also be implemented. The missing values of the efficacy assessment variables will be analyzed using the last-observation-carried-forward (LOCF) method.

A paired *t* test will be used for within-group analysis of the primary and secondary outcome variables. Between-group analysis will be performed using repeated measures ANOVA and the paired *t* test for the primary outcome variable. To measure secondary outcome variables, mean changes in the CHH VAS score, the BT, and the results of the WHOQOL-BREF and CST will be assessed. Repeated measures ANOVA and paired *t* tests will be carried out for the CHH VAS score. A repeated measures ANOVA will also be performed for BT. ANOVA and post hoc analyses will be performed for the WHOQOL-BREF results, and a paired *t* test will be used for the CST results. For the analysis of the Questionnaire of Pattern Identification, ANOVA and post hoc tests will be performed, and for the Questionnaire of Cold Hypersensitivity, Cronbach’s alpha and a correlation analysis will be performed.

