### Trial status

The recruitment of participants has been ongoing since 28 May 2018 and will be completed in May 2020. The currently active protocol version is 2.1 (21 May 2018).

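### Within-arm paired t tests are listed as efficacy analyses, and are the only named type of test for the cold stress test, although the hypothesis is the OKT-minus-placebo difference

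*Protocol article*

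**What the plan says.** All references are to the Protocol article.

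- **Target.** Objectives compares OKT with placebo after 8 weeks. Sample size calculation states H0 as Δ1 − Δ2 = 0, where each Δ is an arm's mean 8-week change in VAS.
- **General method.** Statistical analysis takes as its basic method the "degree of change in the efficacy assessment index between the results of the baseline tests performed before the administration of the test drug" and those at the end of treatment, with significance at P < 0.05.
- **Within arms.** Efficacy says that a paired t "test will be used for within-group analysis of the primary and secondary outcome variables".
- **Between arms.** For the primary outcome: "Between-group analysis will be performed using repeated measures ANOVA and the paired" t test. For the cold stress test (CST), a paired t test is the only method named.
- **Entry and baseline.** Table 1 requires a VAS score of at least 4. Table 4 checks eligibility at visit 1 and measures VAS and skin temperature (BT) at both visit 1 and visit 2 (day 0).
- **Weather.** Discussion grants that "it is possible that changes in weather may have an influence on the outcomes", and adds that "warmer weather is likely to produce better results, and colder weather may negatively affect the results", even with 20 minutes of rest at 24 ± 1 °C before BT and the CST. Under Trial status, recruitment "has been ongoing since 28 May 2018 and will be completed in May 2020".

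**The concern.** A paired t test inside the OKT arm asks whether women on OKT changed. It does not ask whether they changed more than women on placebo, which is the stated hypothesis. The article places these tests under efficacy, gives them the same significance threshold, and nowhere calls them descriptive. For the CST, read literally, no test compares the arms at all. For the primary outcome, one of the two methods named as between-group is a paired test, which does not fit two independent arms, so the contrast rests on the repeated measures ANOVA.

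At stake is what the trial may conclude. A significant improvement in the OKT arm could be presented as efficacy even if placebo improved as much. That matters for a subjective score with an entry threshold, in a condition that the authors expect to move with the weather.

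**Working it through.** **1. What each test estimates.** Write the mean change in the OKT arm as τ + p + r + w and in the placebo arm as p + r + w. Here τ is the drug effect, p placebo response and natural course, r regression to the mean, and w average weather drift. The paired test in the OKT arm tests τ + p + r + w = 0. The arm difference is (τ + p + r + w) − (p + r + w) = τ. Only the second matches H0.

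**2. Sample size.** The article gives 56 per arm with 20% dropout: 45/(1 − 0.20) = 56.25, so 56 fits about 45 completers. It gives no effect size, SD or power, so 56 cannot be rederived in full. I use n = 45 to 56.

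**3. False significance within an arm, with τ = 0.** SD of change (2.0 to 2.5) and total drift (0.5 or 1.0 point) are assumptions; the documents give neither. Noncentrality = drift/(SD/√n), two-sided 5% test.

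| Drift | n, SD | Noncentrality | Critical t | Significant |
|---|---|---|---|---|
| 0.5 | 45, 2.5 | 0.5/(2.5/√45) = 1.34 | 2.015 | 26% |
| 0.5 | 56, 2.0 | 0.5/(2.0/√56) = 1.87 | 2.004 | 45% |
| 1.0 | 45, 2.5 | 2.68 | 2.015 | 75% |
| 1.0 | 56, 2.0 | 3.74 | 2.004 | 96% |

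**4. Regression to the mean from the VAS cut-off.** Assume a normal score, population mean μ = 5 to 6, between-woman SD 1.5 and within-woman SD s = 1.0 to 1.5. With σ² = 1.5² + s² and a = (4 − μ)/σ, the expected fall from a visit 1 baseline is (s²/σ) × φ(a)/(1 − Φ(a)).

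- μ = 6, s = 1.0: σ = 1.803, a = −1.109, fall = (1/1.803) × 0.249 = 0.14.
- μ = 5, s = 1.5: σ = 2.121, a = −0.471, fall = (2.25/2.121) × 0.524 = 0.56.

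With visit 2 as baseline the fall is about 0, provided that within-woman fluctuation is independent between visits.

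**5. Weather.** Simulation with no OKT effect: 56 per arm, blocks of 4, SD of change 2.0, VAS level following a yearly cosine that peaks in mid-winter, 5,000 runs per scenario. Amplitude, block size and enrolment pattern are assumptions. Triplets are for amplitudes 0.5, 1.0 and 1.5 points.

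| Enrolment | Mean drift | OKT arm falsely improved (nominal 2.5%) | Between-arm error (nominal 5%) |
|---|---|---|---|
| Even over two years | about 0 | 2.0, 2.4, 2.1% | 4.3, 3.6, 2.9% |
| Centred on mid-winter | −0.20, −0.39, −0.58 | 10, 30, 53% | 5.0, 4.8, 4.3% |
| Three months after mid-winter | −0.40, −0.80, −1.20 | 33, 84, 99% | 4.6, 4.8, 4.6% |
| Autumn | +0.37, +0.74, +1.11 | about 0% | 5.0, 5.2, 4.9% |

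The between-arm test holds its level throughout without any season term. The within-arm test goes wrong only when enrolment is clustered, and in autumn it errs by hiding improvement.

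**6. What a season term could gain.** If the seasonal part of the 8-week change is a yearly cycle of amplitude A and the residual SD is 2, its share of variance is (A²/2)/(A²/2 + 4). That is 0.125/4.125 = 3% for A = 0.5, 0.5/4.5 = 11% for A = 1.0, and 1.125/5.125 = 22% for A = 1.5.

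**The case against.** The strongest reply is that the trial is randomized 1:1, blinded and concurrently controlled, its hypothesis is between arms, and a between-group analysis of the primary outcome is planned. No sentence says that efficacy will be concluded from a within-arm P value, and an analysis plan that is not shown may label those tests descriptive. This stands as far as the arm comparison goes. It does not answer the text as written, which lists the within-arm tests as efficacy analyses without qualification and gives the CST nothing else.

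A reader might go further and infer that two years of recruitment through all seasons lets weather pass for an OKT effect, or that omitting season biases the trial. The documents do not support either reading. Weather acts on both concurrent arms and cancels in Δ1 − Δ2. Near-even enrolment over two full yearly cycles brings average drift to about zero, and no clustering is reported. Weather is disclosed as a limitation, in cautious terms. A season covariate is something an article may leave to the analysis plan, so its absence is not a fault.

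It is also fair that the drifts of 0.5 and 1.0 point are assumed, and that regression to the mean from the cut-off largely disappears if visit 2 is the baseline. The general method does place baseline before the first dose, but visits 1 and 2 both satisfy that.

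**Conclusion.** The point holds for the within-arm tests and not for the arm comparison. Paired before-after tests at P < 0.05 are part of the efficacy assessment, and for the CST a paired test is the only one named, although the hypothesis is the between-arm difference. With no drug effect, a total drift of 0.5 point from any mix of placebo response, regression to the mean and weather would make the within-arm test significant in 26% to 45% of trials, and a drift of 1.0 point in 75% to 96%, against a nominal 5%. These rates depend on the assumed drift and on an SD of 2.0 to 2.5. Regression to the mean could supply 0.14 to 0.56 point of that drift, but only with visit 1 as baseline. Weather contributes only if enrolment is uneven over the year. The conclusion that a within-arm test does not address Δ1 − Δ2 needs none of these assumptions.

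**What to change.** 1. State that efficacy conclusions rest only on the OKT-minus-placebo difference for every outcome, and name a between-arm comparison for the CST recovery rate.
2. Report within-arm changes as means with 95% confidence intervals, labelled descriptive, without significance claims.
3. Name visit 2 (day 0) as the baseline for change in VAS and BT.
4. Optional, for precision only: add sine and cosine of the randomization date to the between-arm model.

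Items 1 to 3 are wording changes that need no new data and can be settled before the blind is released; the price is the loss of the within-arm P values. Item 4 costs two model degrees of freedom and uses a date that the trial has to hold anyway.

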### Trial status

The recruitment of participants has been ongoing since 28 May 2018 and will be completed in May 2020. The currently active protocol version is 2.1 (21 May 2018).

## Data Availability

The de-identified individual patient data acquired from this study will be available from ([contact]) on reasonable request in December 2022.

## Abbreviations

AE: Adverse event
ALT: Alanine aminotransferase
ANA: Antinuclear antibody
ANOVA: Analysis of variance
AST: Aspartate aminotransferase
BT: Body skin temperature
BMI: Body mass index
BUN: Blood urea nitrogen
CHF: Cold hypersensitivity in the feet
CHH: Cold hypersensitivity in the hands
CHHF: Cold hypersensitivity in the hands and feet
Cr: Creatinine
CRA: Clinical research associate
CRC: Clinical research coordinator
CRF: Case report form
CRO: Contract research organization
CST: Cold stress test
DBP: Diastolic blood pressure
DMC: Data monitoring committee
r-GTP: Gamma-glutamyl transpeptidase
Hb: Hemoglobin
hCG: Human chorionic gonadotropin
IDMC: Independent Data Monitoring Committee
IP: Investigational product
IRB: Institutional Review Board
ITT: Intention-to-treat
KFDA: Korea Food and Drug Administration
KM: Korean medicine
LOCF: Last-observation-carried-forward
OKT: *Onkyeong-tang*
PI: Principal investigator
PP: Per-protocol
RBC: Red blood cell
RCT: Randomized clinical trial
RP: Raynaud’s phenomenon
RR: Recovery rate
SAE: Serious adverse event
SBP: Systolic blood pressure
SOP: Standard operating procedure
TSH: Thyroid-stimulating hormone
VAS: Visual Analog Scale
WBC: White blood cell
WHOQOL-BREF: World Health Organization Quality of Life Scale-abbreviated version
